## Discussion

Botulinum toxin type-A injected in the intended muscle is expected to yield the greatest effect in terms of activities. Protocols for manual intramuscular needle placement should be described in detail and verified to determine the precision of the injection method. Detailed and verified protocols are essential to be able to interpret the results of botulinum toxin type-A treatment studies.

Three relevant articles reporting specific on intramuscular needle placement in live humans failed to provide detailed descriptions of a protocol for intramuscular injection for each individual muscle injection location [16,18,21].

In a randomized control trial two BTX-A intramuscular injection techniques were compared on the functional improvement of the leg of children with CP. The efficacy of BTX-A treatment was compared between intramuscular injections guided by electrical stimulation and intramuscular injections guided by palpation. The statistical analysis of all intramuscular injections of one group were merged [18]. According to the International Classification of Functioning, Disability and Health for Children and Youth (ICF-CY) spasticity of the muscle (body structure) can impair function, which can cause limitations of activities and participation in daily life. There are many factors as health condition, environmental and personal factors which also influence these functional, activity and participation outcomes. Clinical outcomes are blurred by all the factors described above so this methodological choice obscures the results. When there is no clear description of a detailed and verified protocol for intramuscular needle placement merging of intramuscular injections during analysis is not acceptable.

In an other article the author merged data of manual intramuscular needle placements of the soleus muscle and the gastrocnemius muscle and concluded that the percentage of true positive manual needle placements out of all positive needle placements checked by ES was acceptable [16]. Combining muscles and muscle locations does not provide any useful information and does not allow making conclusions about precision or accuracy of manual intramuscular needle placement and verification techniques.

Clarifying statistical terms used in a manuscript is of great importance to make a clear interpretation of the results. In this study protocol the main object of analysis will be the contingent table of intramuscular needle placement checked by PSRM observations versus the corresponding observations with ES (see Table 1). This table will be used to calculate the precision or PPV which is defined as the proportion of true positive needle placements against all positive needle placement results (both true positives and false positives). During BTX-A treatment, BTX-A should be injected only after manual intramuscular needle placement checked positive by PSRM, ES or echo using a verified protocol.

In this study protocol the statistical term accuracy is defined as the proportion of true needle placements (both true positives and true negatives). In a similar article the authors calculated the accuracy which was defined differently as the proportion of positive needle placements checked by ES out of all manual intramuscular injections. Negative manual intramuscular needle placements were not investigated and not checked by ES [16]. One article described intramuscular needle placement based on only landmarks and palpation and in a randomized clinical trial needle placement was based on palpation of the muscle belly after increasing muscle tone by stretching the spastic ankle plantar flexors. Both studies did no use a PSRM technique or an other verification technique to localize the correct needle placement in the target muscle [18,21]. The three methodological methods used do not allow the construction of a contingent table of intramuscular needle placements checked by a needle location technique observations versus observations verified as by means of ES or echo. Nor do they allow the calculation of positive predictive values or precision with their confidence intervals as the main objective for each individual muscle and muscle injection location neither the calculation of the negative predictive value, sensitivity and specificity. This obscures the outcome and allows no clear answer to the question whether intramuscular needle placement is precise for a specific target muscle and a specific injection location.

Additional file 1 provides no guidance of manual intramuscular needle placement depth because it is complicated. The recruited children are aged between 4 and 18 years old and needle depth might depend on the child, age, muscle type, muscle injection location, left and right legs, gender, height, weight and body mass index.

This protocol for manual intramuscular needle placement checked by PSRM is described in detail. If verification of this protocol as by means of ES shows a minimal precision or PPV of 80% with 95% confidence interval and a lower bound of 70% then this protocol is precise and suitable for use in clinical practice of BTX-A treatment in children with spastic cerebral palsy in the lower extremity.

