### Sample size calculation

Each individual muscle injection location of the ADB, ADL, GR, SEM, SET, BF, RF, GL, GM and SO after manual intramuscular needle placement checked by PSRM will be investigated by ES to determine correct needle placement.

The positive predictive value (PPV) or precision is clinically the most relevant parameter to assess the value of this manual intramuscular needle placement checked by PSRM, as it indicates the proportion of the true positive needle placements in the intended muscle against all, true and false, positive needle placements in the intended muscle. If we assume that 90% of the test outcome of manual intramuscular needle placements observed after PSRM is determined to be positive, with α = 0.05 and a power of 80%, then 41 observations of a positive manual intramuscular needle placement will be required for the injection location for each individual muscle. If we assume that approximately 70% of the test outcome of manual intramuscular needle placements observed after PSRM is determined to be positive, with α = 0.05 and a power of 80%, then a total of 60 observations of a positive manual intramuscular needle placement will be required for the injection location for each individual muscle.

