### Statistical analysis

Analyses will be performed using the Statistical Package for the Social Sciences, version 15.0 (SPSS, IBM, New York, USA). The main object of the analysis will be the contingent table of manual intramuscular needle placement checked by PSRM observations versus the corresponding verification as by means of ES observations (see Table 1). This table will be used to calculate the positive predictive value (PPV), with its confidence interval of 95%, as the main objective for each individual muscle and muscle injection location. Positive predictive value or precision is defined as the proportion of the PSRM true positive observations against all the positive observations, both PSRM true positive and PSRM observations. A PPV of 80% with 95% confidence interval and a lower bound of 70% is defined as a minimal acceptable proportion. In addition, negative predictive value (NPV), sensitivity and specificity will also be computed, with their confidence intervals of 95%.

**Table 1 T1:** Contingent table of manual intramuscular needle placement checked by PSRM observations versus the corresponding observations with ES

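### The 80%/70% PPV rule measures how often a PSRM-positive needle is right, but it cannot show that the PSRM check contributes to that precision

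*Protocol article*

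**What the plan says.** The Statistical analysis section sets one standard: "A PPV of 80% with 95% confidence interval and a lower bound of 70% is defined as a minimal acceptable proportion". The Discussion turns it into the study's conclusion: a "minimal precision or PPV of 80% with 95% confidence interval and a lower bound of 70% then this protocol is precise and suitable" for clinical practice. PPV is ES-true needles divided by all PSRM-positive needles. The Sample size calculation calls it "clinically the most relevant parameter to assess the value of this manual intramuscular needle placement checked by PSRM".

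What is to be verified is described in the Background and Methods as a combination of a placement technique and a localizing technique. Under Study procedures every needle, PSRM-positive or PSRM-negative, is left in place and tested by ES. NPV, sensitivity and specificity are reported with 95% intervals, Table 1 has an accuracy cell, and odds ratios are compared with Cochran's homogeneity test. None of these has a threshold.

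The article also speaks about checks as such. The Background asks that techniques for verifying placement be verified themselves. The Discussion makes a positive PSRM, ES or echo check a precondition for injecting, and says of two earlier studies: "Both studies did no use a PSRM technique or an other verification technique to localize the correct needle placement in the target muscle".

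**The concern.** The conclusion depends on two counts only: the PSRM-positive needles and how many of them are ES-true. The PSRM-negative needles are tested but do not enter it. If needle movement says nothing about location, positives are right exactly as often as all needles are. The rule can then be met by good manual placement alone.

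What is at stake is attribution. After a pass, a reader could take needle movement as evidence of location and rank it beside ES or echo, while the study's own negative row shows that the check does not separate right from wrong needles.

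**Working it through.** **Inputs.** The thresholds are PPV at least 80% and lower 95% bound at least 70% (Statistical analysis; Discussion). The Sample size calculation gives 41 PSRM-positive observations per location in a 90% scenario ("then 41 observations of a positive manual intramuscular needle placement will be required for the injection location for each individual muscle") and 60 in a 70% scenario. The interval method is not named, so Wald, Wilson and exact (Clopper-Pearson) were all used. The article assumes no share π of correctly placed needles. Its one figure is 75% for gastrocnemius and soleus in an earlier study cited in the Background, so π is varied from 70% to 90%.

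**The plan's own figures.** The text states "with α = 0.05 and a power of 80"% but gives no null value and no sidedness, so 41 and 60 cannot be reproduced from the stated inputs. That does not prove them wrong; they are taken as given.

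**Step 1: an uninformative check.** PPV = π·Se / [π·Se + (1−π)(1−Sp)]. If the check carries no information, Se = 1−Sp and this reduces to PPV = π.

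**Step 2: counts needed to pass.**
- n = 41: 34 (Wald: 0.829 − 1.96·√(0.829·0.171/41) = 0.714) or 35 (Wilson or exact).
- n = 60: 49 (Wald or Wilson) or 50 (exact). With 48/60 the Wald bound is 0.80 − 1.96·√(0.80·0.20/60) = 0.699, which just fails.

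**Step 3: chance of passing when the check is uninformative.** P(X ≥ x), with X ~ Binomial(n, π) and independent needles:

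| π | 34/41 | 35/41 | 49/60 | 50/60 |
|---|---|---|---|---|
| 70% | 4.6% | 1.9% | 3.0% | 1.4% |
| 75% | 16.1% | 8.3% | 14.8% | 8.6% |
| 80% | 40.7% | 26.1% | 44.9% | 32.3% |
| 85% | 73.4% | 58.1% | 81.9% | 71.6% |
| 90% | 95.2% | 89.0% | 98.5% | 96.6% |

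**Step 4: two studies that the rule cannot tell apart.** Take 100 needles, 90 of them PSRM-positive, with PPV 90%: 81 positives are ES-true and 9 ES-false.
- Informative check: all 10 negatives are ES-false. Sensitivity is 81/81 = 100%, specificity 10/19 = 53%, and 81% of all needles are correct.
- Useless check: 9 of 10 negatives are ES-true. Sensitivity is 81/90 = 90%, specificity 1/10 = 10%, and 90% of all needles are correct.

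Both pass with the same probability (89% at 35/41). In general π = q·PPV + (1−q)(1−NPV). With q = 0.9, PPV = 0.9 and a check that is at least uninformative, π lies between 0.81 and 0.81 + 0.1·0.9 = 0.90. The check can then account for at most 9 points of the 90%.

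**Step 5: can the planned secondary measures settle it?** Read literally, the scenarios describe the share of PSRM-positive needles ("If we assume that 90% of the test outcome of manual intramuscular needle placements observed after PSRM is determined to be positive"). On that reading:
- 90% scenario: 41/0.9 − 41 = 4.6, about 5 negatives per location. An NPV of 3/5 has an exact 95% interval of 15% to 95%, so NPV is very imprecise.
- 70% scenario: 60/0.7 − 60 = 25.7, about 26 negatives. An NPV of 3/26 has an exact interval of 2% to 30%, which is informative.
- Cochran's test asks whether odds ratios are equal across strata. Odds ratios of 1 at every location would satisfy it.
- The factor analysis concerns false positives only.
- Table 1 labels PSRM-negative/ES-true as true negative and PSRM-negative/ES-false as false negative, which is reversed. Secondary measures computed from those labels would be wrong.

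**The case against.** The strongest reply is that the rule does what it is meant to do. The object of verification is the combined protocol, and its precision is defined as PPV. If 85-90% of needles are correct and the check is useless, the true PPV is 85-90%, above the 80% standard, and calling the protocol precise is right. A reader might take the 58-98.5% in the table as a false-positive rate; the article does not support that. Nor does it state outright that PSRM improves placement: the Discussion's conclusion is about the protocol as a whole. PPV is also the relevant quantity for needles accepted after a positive check. High shares of correct needles are assumed here, and the article's only figure, 75%, gives 8-16%. Negatives are tested, the full table is reported, and in the 70% scenario NPV would expose a useless check.

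All of that stands, and it limits the point to attribution. It does not remove it. The article asks that verification techniques be verified and places a positive PSRM check beside ES and echo, yet no stated criterion or comparison shows whether the check separates right from wrong needles. Odds ratios are planned, but the only stated use is to compare them with each other.

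**Conclusion.** The point holds in a limited form. The 80%/70% rule validly measures how often a PSRM-positive needle of the combined protocol is right; it cannot show that the PSRM check contributes. With an uninformative check the rule passes with probability from 1-5% (70% of needles correct) to 89-98.5% (90% correct). This rests on assumed shares, independent needles, and the stated 41 or 60 positives.

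Two stronger readings should be avoided. The rule does not wrongly accept an imprecise protocol at the high shares. The data to judge the check are not missing either: they are recorded for every needle but tied to no criterion, and per location they are thin in the 90% scenario. The matter is a gap between the rule and what a reader may conclude about PSRM, and it is cheap to close.

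**What to change.** In the Statistical analysis section and Table 1:
- Report at each location the ES-true proportion among all placements, with its 95% interval, beside the PPV.
- Add one location-stratified estimate of the association between PSRM result and ES result, with a 95% interval that allows for several needles per child. It can be a Mantel-Haenszel risk difference or a common odds ratio built from the odds ratios already planned. Stratifying keeps locations separate and so respects the Discussion's objection to merged data.
- Correct the two PSRM-negative labels in Table 1 before any secondary measure is computed.

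In the Discussion, let the 80%/70% rule support only the statement that PSRM-positive placements are precise at that location. Attribute precision to the PSRM check only if the stratified contrast excludes no association (lower 95% bound above 0 for a risk difference, above 1 for an odds ratio). Otherwise state that the precision may reflect manual placement alone.

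The cost is two summaries from data already recorded and some rewording, with no extra patients or procedures. The downside is that the claim for PSRM may become narrower than the claim for the combined protocol.

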## Abbreviations

ADB: Adductor brevis muscle; ADL: Adductor longus muscle; ASA: American society of anesthesiologists; BF: Biceps femoris muscle; BMI: Body mass index; BTX-A: Botulinum toxin type-A; CP: Cerebral palsy; ES: Electrical stimulation; GL: Gastrocnemius lateralis muscle; GM: Gastrocnemius medialis muscle; GR: Gracilis muscle; ICF-CY: International classification of functioning, disability and health for children and youth; METC: Medical research ethics committee; NPV: Negative predictive value; PPV: Positive predictive value; PSRM: Passive stretching and relaxing of the target muscle; RF: Rectus femoris muscle; SEM: Semimembranosus muscle; SET: Semitendinosus muscle; SO: Soleus muscle; WMO: Dutch medical research involving human subjects act.
